## 1. Introduction

The life expectancy of individuals with severe mental disorders is estimated to be 20 [1] to 30 [2] years shorter than that of the general population, with evidence suggesting that this disparity has widened in recent decades [3].

Cardiovascular and metabolic diseases are the main causes of death in this population group [4], and having a diagnosis of psychosis is considered a risk factor for the development of these diseases [5]. It is also a risk factor for death from cardiovascular or cerebrovascular events [6].

Metabolic syndrome (MetS), a common cause of cardiovascular and metabolic diseases, develops in one out of every three individuals experiencing psychosis, nearly doubling the odds compared to the general population [7,8]. MetS includes central obesity, increased fasting glucose, dyslipidemia, and hypertension, with insulin resistance playing a central role in various tissues of the body [9,10]. Different definitions have been proposed with similar criteria to diagnose MetS, which involve waist circumference, blood triglyceride levels, HDL cholesterol, fasting glucose, and systolic and diastolic blood pressure biomarkers [11,12,13].

In people who experience psychosis, one of the causes of MetS is the deregulation of glucose metabolism induced by antipsychotic treatment, especially second-generation antipsychotics [14]. In people who have experienced a first psychotic episode, the first year of treatment is crucial for weight gain and the establishment of metabolic alterations [15], with early insulin resistance being a predictor of weight gain and increased waist circumference [16], related to the alteration of hunger regulation [17]. With some exceptions such as Ziprasidone and Lurasidone, all antipsychotics cause significant weight variation, with a greater effect seen in the case of Clozapine and Olanzapine [18].

There is also evidence suggesting that the altered metabolic parameters may not only be due to antipsychotic treatment [19], but also involve other systems beyond the central nervous system in individuals with psychosis [20]. Poor dietary habits [21] or sedentary behavior, closely related to the negative symptoms of psychotic processes such as a lack of motivation or cognitive deterioration, have also been associated with MetS. Additionally, low economic income has been correlated with worse metabolic parameters [22].

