### 2.4. Randomization and Treatment Allocation

Subjects will be selected during their psychiatry consultations following the stabilization of their pathology. If they meet the inclusion/exclusion criteria, they will be informed about the possibility of participating in the study, including its content and purpose. After being provided with an informed consent form and signing it, they will be randomly assigned to either the experimental or control group. Randomization will be conducted using a computer-generated random list. As participants are offered the opportunity to join the study, they will be assigned a number from the list in sequential order. The psychiatrist who refers the participants will not have access to the randomization list, ensuring allocation concealment. On the other hand, the psychiatrist responsible for administering the psychometric scales will be blinded to the intervention.

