### 2.7. Instruments and Variables

Sociobiographic data will be collected, including sex, age, marital status, living arrangement, educational level, medical diagnosis, time since the beginning of treatment, substance use, antipsychotic type and dose, mood stabilizer use, and whether patients are assisted by a primary caregiver (considered as such if they assist in 4 of the first 6 consultations).

The primary outcome will be weight loss, with a reduction of 5% considered clinically significant [38]. Secondary outcomes will include the establishment or non-establishment of metabolic syndrome according to the International Diabetes Federation (IDF) criteria [12], which consist of abdominal obesity (abdominal circumference ≥ 94 cm in men and ≥80 cm in women) plus two of the following four factors: (i) elevated blood triglycerides (≥150 mg/dL or treatment for it); (ii) decreased HDL-c (<40 mg/dL in men and <50 mg/dL in women); (iii) high blood pressure (systolic blood pressure ≥ 130 mmHg and diastolic blood pressure ≥ 85 mmHg or antihypertensive treatment); and (iv) elevated fasting glucose (≥100 mg/dL or previous diagnosis of type 2 diabetes).

Anthropometric variables (weight, height, BMI, waist circumference) and vital signs (resting blood pressure) will be measured using calibrated equipment provided by the hospital.

Laboratory values (fasting blood glucose, glycosylated hemoglobin, triglycerides, HDL, HDL/LDL ratio, C-reactive protein) will be collected in accordance with hospital policy.

To measure psychopathology, the Positive and Negative Syndrome Scale (PANSS) will be used. This scale consists of 30 items divided into three subscales: positive, negative, and general. The positive subscale measures symptoms such as hallucinations and delusions, the negative subscale measures symptoms such as flat affect and lack of motivation, and the general subscale measures symptoms such as agitation and hostility [37].

Depressive symptoms will be assessed using the Hamilton Depression Rating Scale (HAM-D), which consists of 17 items, with higher scores indicating greater severity of symptoms [39].

The EuroQol-5D (EQ-5D) scale will be used to evaluate a person’s subjective well-being in relation to their health. The scale consists of five dimensions: mobility, self-care, usual activities, pain/discomfort, and anxiety/depression [40].

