### 2.8. Statistical Analysis

Categorical variables will be described as frequencies and percentages, while quantitative variables will be described as means and standard deviation (or medians and interquartile ranges where appropriate). Categorical variables will be compared using chi-square analysis or Fisher’s exact test, and quantitative variables will be compared using Student’s *t*-test, ANOVA, or the Mann–Whitney rank-sum test.

To compare changes in outcome variables between groups and over time, a multivariate mixed-effects model with repeated measures (linear or logit, depending on the characteristics of the variable) will be applied. Statistical significance will be assumed if the two-sided *p*-value is <0.05. The main analysis will assess the association between the study group and significant weight loss, defined as losing 5% of the original body weight.

To account for the potential effect of antipsychotics on weight and metabolic parameters, antipsychotics will be categorized as weight-increasing, weight-sparing, or as having non-conclusive effects. Sensitivity analyses will be conducted to examine the effect of each category on the outcomes. Categorization will be based on a review of previous evidence [42]. The use of weight-increasing antipsychotics in combination with weight-sparing antipsychotic use will be coded as weight-increasing antipsychotic use. The cumulative exposure of chlorpromazine-equivalent doses will then be calculated for each antipsychotic category in every patient [43].

Sensitivity analyses will also be conducted for each of the variables included in the previous section.

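### The antipsychotic weight category, which the protocol treats as a driver of weight, is given a role only in sensitivity analyses; adding it at randomisation, with baseline weight, to the main model would bring a modest gain at almost no cost

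*Protocol article*

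**What the plan says.** The Introduction (section 1) presents antipsychotic treatment as a cause of weight change. With some named exceptions, "all antipsychotics cause significant weight variation, with a greater effect seen in the case of Clozapine and Olanzapine". Section 2.7 lists "antipsychotic type and dose, mood stabilizer use" among the variables collected, without fixing the time point.

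Section 2.4 describes allocation in one step: "Randomization will be conducted using a computer-generated random list". Numbers are then used in sequence. No strata are mentioned.

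Section 2.8 sets out the analysis. For outcomes over time, "a multivariate mixed-effects model with repeated measures (linear or logit, depending on the characteristics of the variable) will be applied"; the model terms are not listed. The main comparison is then defined: "The main analysis will assess the association between the study group and significant weight loss, defined as losing 5% of the original body weight". The next paragraph turns to the drugs: "To account for the potential effect of antipsychotics on weight and metabolic parameters, antipsychotics will be categorized as weight-increasing, weight-sparing, or as having non-conclusive effects". The role it gives these categories is: "Sensitivity analyses will be conducted to examine the effect of each category on the outcomes". It adds that "The cumulative exposure of chlorpromazine-equivalent doses will then be calculated for each antipsychotic category in every patient". The remaining variables of section 2.7 are also sent to sensitivity analyses.

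Table 1 shows weight measured at enrolment and at allocation.

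**The concern.** The protocol names one factor as influential for its own primary outcome, collects it, and builds a three-level variable from it in order to allow for it. The only place it then assigns to that variable is outside the main analysis. As described, allocation does not balance the factor either. So this goes further than a covariate list left unwritten: the text says where the factor will be used.

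Two things are at stake. First, part of the outcome variation that a pre-treatment variable could explain stays in the main comparison and costs power. Second, if the arms differ by chance in their share of weight-increasing drugs, the main estimate carries that difference, and only a secondary analysis would allow for it. Baseline weight is in a similar position: it is measured, but its only stated part in the main outcome is as the denominator of the percentage.

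**Working it through.** **Inputs from section 2.9.** Difference 5 points of percent weight; SD 7.5; two-sided 5%; 80% power; 74 evaluable; 88 recruited, 44 per arm.

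**Inputs not in the documents (assumed).** Prevalence of the weight-increasing category 50% (30% to 70% for imbalance); gap g in mean percent weight change between two categories of 3, 5 or 7 points. The SD of 7.5 is taken as the total within-arm SD.

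**1. The plan's own figure.** Two-sample t-test, noncentral t, noncentrality 5 / (7.5 × √(2/n)):
- n = 36 per arm: power 79.7%
- n = 37 per arm: power 80.8%

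So 37 per arm, or 74 in total, reproduces the stated number. The sample size is therefore that of an unadjusted comparison of continuous percent change.

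**2. Variance explained by the category.** For a binary category at 50% prevalence, R² = 0.25 × g² / 7.5², and the residual SD is 7.5 × √(1 − R²).

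| Gap g | R² | Correlation | Residual SD | SE of difference, 37 per arm |
|---|---|---|---|---|
| none | 0 | 0 | 7.50 | 1.74 |
| 3 | 0.25 × 9 / 56.25 = 0.04 | 0.20 | 7.35 | 1.71 |
| 5 | 0.25 × 25 / 56.25 = 0.11 | 0.33 | 7.07 | 1.64 |
| 7 | 0.25 × 49 / 56.25 = 0.22 | 0.47 | 6.63 | 1.54 |

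**3. Power, continuous percent change.** Same formula with the residual SD and 2 degrees of freedom deducted: 80.8% unadjusted; 82.3% at a 3-point gap (+1.5); 85.1% at a 5-point gap (+4.3).

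**4. Power, binary 5% loss (the stated main outcome).** Simulation under the same normal model: control mean 0, intervention mean −5, SD 7.5. Responders are then about 25% (Φ(−5/7.5) = 0.252) against 50%. One binary covariate, 37 per arm, single visit, 8,000 trials per gap, likelihood-ratio test of group in logistic regression without and with the covariate.

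| Gap | Unadjusted | Adjusted | Gain |
|---|---|---|---|
| 3 | 60.3% | 61.1% | about 1 point |
| 5 | 60.9% | 64.2% | about 3 points |
| 7 | 59.9% | 66.9% | about 7 points |

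The small differences in the unadjusted column are simulation noise.

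**5. Chance imbalance.** Two independent binomials, 44 per arm. At 50% prevalence the SD of the difference in shares is √(2 × 0.25 / 44) = 10.7 percentage points. Exact probabilities of an absolute difference of at least:
- 10 points: 29% to 34% over prevalences of 30% to 70%
- 15 points: 17% at 50% prevalence
- 20 points: 5% to 7%, the 7% being at 50% prevalence

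At 35 per arm (88 less 20%, halved), a 20-point difference has a chance of 9% to 12%.

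**6. Shift of the unadjusted estimate.** Imbalance × gap: 0.20 × 3 = 0.6 points and 0.20 × 5 = 1.0 point. Against the target of 5 this is 12% to 20%; against the SE of 1.74 it is 0.34 to 0.57 of a standard error.

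**The case against.** The strongest reply is that nothing here is invalid. Under randomisation the unadjusted comparison is unbiased, and its standard error already reflects chance imbalance; simulated type I error stays at 4% to 5%. That stands. A reader might infer that the main result is biased or that an error goes uncorrected, and the documents do not support this.

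Second, the model is called multivariate and its terms are not listed, so a full protocol or analysis plan may add covariates. This also stands in part: one cannot say that section 2.8 expressly excludes the category. What remains is that the only role it gives the category is in sensitivity analyses.

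Third, the exposure that section 2.8 quantifies is cumulative dose, which can accrue after randomisation, and no baseline category is defined. For cumulative exposure a sensitivity analysis is the right place. The point concerns the category at randomisation, a variable that section 2.8 would have to define.

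Fourth, the predictive strength is unknown. Patients may enter up to 5 years after a first episode and after stabilisation, so part of any drug-related gain may already sit in baseline weight. A 5-point gap is as large as the trial's whole target effect. This limits the size of the gain and is why a range is given.

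Three further readings go too far:
- That precision is lost on the logit scale. The standard error of the log odds ratio rises on adjustment (for example from 0.51 to 0.55 at a 5-point gap), because the conditional odds ratio is a different and larger quantity. The gain there is in power only.
- That a 1-point shift has a 17% chance. That figure belongs to an imbalance of 15 points or more; the shift of 1 point needs 20 points, with about a 7% chance, and a 5-point gap.
- That nothing says which result stands if the two disagree. Section 2.8 labels one analysis as the main one, and that settles the order.

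**Conclusion.** The concern holds as a matter of efficiency, not validity. The protocol treats antipsychotic type as a driver of weight, yet assigns it a role only outside the main analysis and mentions no stratification by it. Using it at randomisation in the main model would be the better method.

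The gain is modest. On the continuous scale it is about 1.5 to 4 points of power for gaps of 3 to 5 points. On the binary outcome that section 2.8 makes the main one, it is about 1 to 7 points for gaps of 3 to 7 points, from a base near 60%. Adjustment would also remove a conditional shift of 0.6 to 1.0 points in the less likely event of a 20-point imbalance. All of this rests on an assumed gap and prevalence. The binary figures further rest on a control mean of zero, normal errors, and a single-visit model with one binary covariate, which is simpler than the repeated-measures model planned. With power on the binary outcome this low, a small gain that needs no more participants is worth prespecifying.

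**What to change.** In section 2.8, or in the analysis plan, state before outcome data are examined that:
- the main weight-loss model includes, beside study group, the antipsychotic weight category at randomisation (the three levels already defined) and baseline weight;
- sparse levels of the category are merged by a rule fixed in advance;
- continuous outcomes are adjusted for their own baseline value;
- the unadjusted model and cumulative exposure after randomisation are kept as sensitivity analyses, and no post-randomisation exposure enters the main model;
- the marginal (standardised) difference in responder proportions is reported beside the conditional odds ratio.

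**Cost.** A few sentences. Antipsychotic type and baseline weight are already collected, so no visits or participants are added; section 2.7 should say that antipsychotic type is recorded as of randomisation. The statistical price is a few model degrees of freedom with few responders: under the 25% against 50% scenario, 37 × 0.252 + 37 × 0.50 ≈ 28 per visit. Sparse cells and convergence therefore deserve attention, which is why the merging rule has to be fixed in advance. The conditional odds ratio also cannot stand alone and needs the marginal estimate beside it.

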### 2.9. Power and Sample Size

We aim to detect a 5% difference in total weight, considering this to be clinically significant [36]. Using a power of 80%, a bilateral alpha of 5%, and assuming a standard deviation of 7.5% in an area where evidence is limited (weight loss in people who have experienced a first psychotic episode). A sample size of 74 participants will be required to detect this difference. Assuming a dropout rate of 20%, we aim to recruit a total of 88 participants, with 44 in each group.

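### The recruitment target of 88 does not cover the plan's own 20% drop-out: it leaves about 70 participants, not the 74 required

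*Protocol article*

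**What the plan says.** Section 2.9 (Power and Sample Size) of the protocol article gives all the inputs. The target effect is a difference of five percentage points in body weight: "We aim to detect a 5% difference in total weight, considering this to be clinically significant". The error rates are given as "Using a power of 80%, a bilateral alpha of 5" percent. The variability is set by "assuming a standard deviation of 7.5% in an area where evidence is limited". From these the section concludes: "A sample size of 74 participants will be required to detect this difference". It then allows for losses: "Assuming a dropout rate of 20%, we aim to recruit a total of 88 participants, with 44 in each group". No formula is shown for either step, and no other section of the article restates or corrects the recruitment target.

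**The concern.** A drop-out rate is a share of those recruited. To finish with a required number after losing a fraction d, that number is divided by (1 − d). Multiplying it by (1 + d) always gives too few. The step from 74 to 88 looks like the multiplication, so the three figures in the section (74 needed, 20% lost, 88 recruited) cannot all be true.

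At stake is whether the trial reaches the number it says it needs, and so the 80% power it claims, under its own assumptions. There is almost no slack, because 37 per arm is the smallest whole number that reaches 80%. Drop-out is also a realistic prospect. Section 2.3 defines it broadly (missed consultations, admission for relapse, symptom scores above a threshold, aggressive behaviour), and follow-up runs to 12 months.

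**Working it through.** **Inputs, all from section 2.9**

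- Difference to detect: 5 percentage points of body weight
- Standard deviation: 7.5 percentage points
- Two-sided alpha: 5%; power: 80%
- Required before drop-out: 74, taken as 37 per arm at 1:1 (the arms are stated to be equal at recruitment)
- Drop-out: 20%
- Recruitment target: 88, that is 44 per arm

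**Step 1. Reproduce the 74.** The standardised difference is 5 / 7.5 = 0.667. A two-sample t-test (noncentral t distribution, two-sided alpha 0.05, power 0.80) needs 36.3 per arm, so 37 per arm and 74 in total. This matches the stated figure exactly. The normal approximation gives 36 per arm, 72 in total. The starting number is sound, so the problem lies only in the allowance for drop-out.

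**Step 2. Apply the 20% drop-out.**

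- In total: N / (1 − d) = 74 / 0.8 = 92.5, so 93 recruits.
- Per arm: 37 / 0.8 = 46.25, so 47 per arm and 94 in total.
- The stated 88 is 5 below 93 and 6 below 94.

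**Step 3. Find what gives 88.** Multiplying gives 74 × 1.2 = 88.8 in total and 37 × 1.2 = 44.4 per arm. Rounded down, these are the stated 88 and 44. This route is inferred from the numbers. The finding does not depend on it.

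**Step 4. Work forward from 88.**

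- Remaining after a 20% loss: 88 × 0.8 = 70.4 in total, 44 × 0.8 = 35.2 per arm. This is about 70, or 35 per arm, and 4 short of 74.
- Largest drop-out at which 88 recruits still leave 74: 1 − 74/88 = 15.9%.

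**Step 5. Power at the numbers that remain** (difference 5, SD 7.5, two-sided alpha 0.05):

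| Per arm | t-test | Normal approximation |
|---|---|---|
| 35 | 78.5% | 79.6% |
| 36 | 79.7% | 80.7% |
| 37 | 80.8% | 81.8% |

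The t-test column is the one to read, because it is the method that reproduces the 74. The loss from 37 to 35 per arm is 80.8 − 78.5 = 2.3 percentage points.

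**The case against.** **The consequence is slight.** Power of 78.5% is 1.5 points below nominal, and the section itself concedes that its standard deviation rests on limited evidence. An SD of 7.36 in place of 7.5 would restore 80% power with 35 per arm. This stands. The shortfall lies well inside the uncertainty of the plan's own input and is not a failure of the design.

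**Drop-outs may still contribute data.** Section 2.8 plans a mixed-effects model with repeated measures, Table 1 schedules weight at every visit, and section 2.3 defines drop-out by attendance and clinical events, not by absence of outcome data. The figure of 70 and the 78.5% are therefore a complete-case, two-sample reading. That label is fair. It does not rescue the 88, because adding recruits for drop-out already treats drop-outs as lost, and the allowance must then be computed consistently.

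**A base of 72 would bring the figures closer.** From the normal approximation, 72 / 0.8 = 90, which is near 88. But the section states 74, and 88 is still below 90, as 70 is below 72.

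**Rounding.** Rounding can turn 88.8 into 88, in the unfavourable direction. It cannot turn 92.5 into 88.

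**Conclusion.** The point holds. At the stated 20% drop-out, 88 recruits leave about 70 participants where the section requires 74. The correct target is 93, or 94 with equal arms. Power falls to 78.5% from the 80.8% that 74 would give.

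The recruitment shortfall is simple arithmetic on three figures given side by side. The power figures assume a two-sample t-test on the continuous weight difference, the stated SD of 7.5, equal arms with equal losses, and no information from drop-outs. Under those assumptions the error is definite but small. It should be corrected because the stated target and the stated drop-out tolerance cannot both be relied on.

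**What to change.** Correct the last sentence of section 2.9 in one of three ways:

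1. **Keep 88 and restate the power.** With 88 recruited and 20% drop-out, about 70 participants remain (35 per arm), with power of about 78.5% by two-sample t-test.
2. **Keep 88 and restate the tolerance.** With 88 recruited, 74 remain provided that drop-out does not exceed about 16%.
3. **Keep 74 and 20% and raise the target.** Recruit 94, that is 47 per arm, which leaves 94 × 0.8 = 75.2.

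The first two cost one sentence and a slightly less favourable figure, with no extra participants. The third costs six more recruits. Whichever is chosen, the section should show the division by 0.8 so that the step can be checked.

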### 2.10. Safety Assessments

Although no adverse effects are anticipated from the intervention, if they do occur, they will be recorded to the patients’ medical records and evaluated. In the event that risks are observed for participants or others, participation in the study will be suspended in those specific cases.

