## 2. Methods

### 2.1. Design

This protocol is designed as an open-label, randomized clinical trial involving a group of patients in a first-episode psychosis (FEP) program, who will attend a series of nursing consultations focused on healthy habits aimed at addressing metabolic syndrome, in addition to their usual follow-up. The control group will consist of patients from the same program who will attend only routine nursing evaluation consultations.

The first author ([name]) will conduct the nursing consultations, based on a previously developed guide that structures and serves as a reference framework for the intervention.

This study was retrospectively registered on Clinical Trials—NCT06650943.

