### 2.3. Participants

The inclusion criteria for the present study will include the following: (a) patients admitted to the EIP due to a (b) FEP within the last 5 years, (c) with a diagnosis of psychosis from the F2 spectrum or an affective disorder with psychotic symptoms as per the ICD-10 [36].

Exclusion criteria will include (a) cognitive inability to learn or a comorbid diagnosis of an intellectual disability that interferes with the study procedures, (b) a comorbid diagnosis of neurological pathology, (c) the presence of language or comprehension alterations that prevent accurate data collection, (d) being prescribed a hypoglycemic drug before or during the study, or (e) refusal to participate. No patients will be excluded based on their special dietary needs (e.g., celiac disease, veganism, special diets) or a diagnosis of MetS before the start of the intervention. The primary consideration will be the individual’s desire to improve their weight or metabolic status. A participant will be considered a drop-out if they miss 2 or more of the first 6 consultations, are admitted to the hospital due to psychotic relapse, and/or experience psychopathological decompensation characterized by a score of 5 or higher on items P1 (delusions), P2 (conceptual disorganization), P3 (hallucinatory behavior), P6 (suspiciousness, persecution), P7 (hostility), and/or G8 (uncooperativeness) on the Positive and Negative Symptoms Evaluation Scale (PANSS) [37], and/or exhibit clinically significant self-directed or outwardly aggressive behavior.

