### 2.5. Intervention

The study intervention will consist of a series of 8 nursing consultations with a specialized mental health nurse, who is trained in teaching healthy habits to individuals with psychosis and understands the unique factors influencing this group. The nurse will also be skilled in using the therapeutic relationship as a tool for habit modification.

During the first two months, 4 consultations will be held, focusing on educating patients about dietary habits based on the carbohydrate–insulin theory of obesity and physical activity, following a manualized intervention previously designed by a team composed of a mental health nurse, a nutrition and dietetics graduate, and a psychiatrist. This guide has been designed based on the consensus report of the American Diabetes Association for nutrition therapy for diabetes and prediabetes [26], as well as incorporating insights from clinical experience with individuals with a first episode of psychosis. The next two visits will take place 3 and 4 months after the first visit, respectively. Visit 7 will be held after 6 months to evaluate the intervention’s effectiveness, and visit 8 at 12 months. During all visits, weight will be monitored as a reinforcement element.

At the beginning of the study, and at 6 and 12 months from the start of the intervention, a battery of tests will be conducted, including analytical samples, vital signs, anthropometric measurements, and scales to assess psychopathology, quality of life, and level of physical activity.

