As shown in Table 1, each consultation will have a central topic. The first session will cover the objectives of the intervention, emphasizing the achievement of greater well-being and the prevention of various cardiometabolic illnesses. The second session will explain the importance of food quality over calorie counting. In the third session, patients will be educated on identifying different macronutrients, their functions, and the relationship between insulin and weight regulation. The fourth session will provide various tips and types of diets to help patients incorporate this model into their own situations. The fifth session will focus on physical activity, highlighting the most efficient types for fat loss and the improvements that patients can implement. The sixth consultation will involve a follow-up to assess any difficulties in making changes and refine strategies to overcome them. After this consultation, the intervention will be concluded. The overall approach will focus on the progressive and flexible acquisition of habits, aiming to integrate changes into the patient’s daily life. This will occur within the therapeutic relationship established between the mental health nurse and the patient, utilizing a psychoeducational and non-blaming approach.

The consultations will use a previously developed guide, which will be provided to patients to allow them to review the information discussed during the sessions.

To improve adherence to the intervention protocol, participants will be called by phone two business days before their visits.

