### 2.6. Control Group

Both the intervention group and the control group will continue their usual follow-ups within the EIP, attending consultations with their reference psychiatrist and receiving pharmacological or psychotherapeutic treatment as they did before the intervention. The control group will not receive any specific nursing consultations (beyond the administration of long-acting injectable antipsychotics where appropriate) or dietary or lifestyle advice during the follow-up. If patients in the control group require treatment or assistance for metabolic problems, they will be referred to primary care or endocrinology professionals, as was done previous to the intervention implementation.

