### 2.11. Data Collection and Management

A notebook will be created to record the data obtained in an orderly manner for each subject over time, and this data will subsequently be transferred to a unified database designed for this purpose. The samples and associated data will be coded. Therefore, the handling, communication, and transfer of such data will be governed by Organic Law 3/2018 of December 5th, on the protection of personal data and the guarantee of digital rights. Participants may access, correct, or cancel their data at any time. Only the research team and the health authorities, who are duty-bound to maintain confidentiality, will have access to all the data collected by the study, which will be stored securely and guarded by the principal investigator (PI). This study will be conducted in accordance with the Declaration of Helsinki and the rules of Good Clinical Practice. Participants and/or guardians will also be informed that this intervention is not part of the standard service offering and that any subject may withdraw from the study at any time upon request.

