## Figures and Tables

**Table 1 nursrep-15-00003-t001:** Schedule of enrolment, interventions and assessments.

	Enrolment	Allocation	Post-Allocation							
TIMEPOINT	0	0	w 1	w 3	w 5	w 8	w 12	w 16	w 24	w 48
ENROLMENT:										
Eligibility screen	X									
Informed consent	X									
Allocation		X								
INTERVENTIONS:										
Mental health nurse consultation			X	X	X	X	X	X		
Aims and giving patients handbook			X							
Calorie counting errors and food to avoid				X						
Insulin and fats, proteins and CH					X					
Tips and feeding protocols						X				
Physical activity type							X			
Follow-up and counselling								X		
Treatment as usual										
ASSESSMENTS:										
Weight	X	X	X	X	X	X	X	X	X	X
Anthropometric variables (height, blood pressure, lab test…)			X						X	X
Scales (PANSS, HAM-D, EQ-5, IPAQ)			X						X	X

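### Section 2.10 suspends study participation, not only the nursing consultations, when a risk is observed, and nothing keeps the participant in the 6- and 12-month assessments (minor, cheap to reword)

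*Protocol article*

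**What the plan says.** Section 2.10 expects no adverse effects from the intervention, has any that occur recorded and evaluated, and then sets the rule: "In the event that risks are observed for participants or others, participation in the study will be suspended in those specific cases". It gives no duration for the suspension and does not limit it to the consultations.

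The assessments have their own timetable. Section 2.5 says of the sixth consultation: "After this consultation, the intervention will be concluded". Table 1 puts that consultation at week 16. The same section sets the outcome measurements: "At the beginning of the study, and at 6 and 12 months from the start of the intervention, a battery of tests will be conducted". In Table 1 the row beginning "Scales (PANSS, HAM-D, EQ-5, IPAQ" and the row for blood pressure and laboratory tests are marked at weeks 1, 24 and 48. Weight is marked at every column, including weeks 24 and 48.

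Two other sections deal with leaving the trial. Section 2.3 lists drop-out events: missed consultations, relapse admission, high scores on named PANSS items, and participants who "exhibit clinically significant self-directed or outwardly aggressive behavior". Section 2.11 covers voluntary withdrawal: "any subject may withdraw from the study at any time upon request".

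**The concern.** Stopping a treatment and stopping follow-up are separate decisions. A risk seen in a participant may be a good reason to end the dietary and activity sessions. It is seldom a reason to stop weighing that person or drawing a scheduled blood sample. The rule as worded does not distinguish the two, so outcome values already on the schedule could go missing for a reason tied to the participant's condition. The PANSS, HAM-D and laboratory follow-up would then be lost in the very people in whom a risk had been noticed.

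**Working it through.** Section 2.10 carries no figure of its own, so the check is of wording and schedule.

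**1. What is suspended.** Section 2.10 names study participation. Sections 2.5, 2.11 and Table 1 contain no statement that a suspended participant remains in follow-up.

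**2. What one suspension costs.** Inputs from Table 1: batteries at weeks 1, 24 and 48 (3 occasions, 2 of them after baseline); evaluation weights at weeks 24 and 48.

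| Suspension | Batteries lost | Evaluation weights lost |
|---|---|---|
| Starts before week 24, not lifted | 2 of 3 (both post-baseline) | weeks 24 and 48 |
| Starts between weeks 24 and 48, not lifted | 1 of 3 | week 48 |
| Lifted before week 24 | 0 of 3 | none |

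Weights taken up to the suspension remain, and the repeated-measures mixed model in Section 2.8 can use them. It has no such help for the laboratory values and scales, which have no post-baseline measurement before week 24.

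**3. Which cases the rule adds.** Relapse admission, PANSS decompensation and aggressive behaviour are already drop-out under Section 2.3, whose exclusion (d) also covers a hypoglycemic drug prescribed during the study. Voluntary withdrawal falls under Section 2.11. Only the remaining risks belong to this point.

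**4. Scale, as an assumption.** The documents give no suspension rate. With 88 participants there are 88 × 2 = 176 scheduled 6- and 12-month occasions. If 1 participant is suspended, 0 to 2 of 176 are lost (0 to 1.1%). If 4 are suspended, 0 to 8 of 176 are lost (0 to 4.5%). The range of 1 to 4 is illustrative only.

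**5. Whether the drop-out allowance covers it.** Section 2.9 needs 74 evaluable participants. This reproduces: a two-sided t-test at 5% with 80% power, difference 5 and SD 7.5 needs 36.3, so 37 per arm and 74 in total. Recruitment is 88, a margin of 88 − 74 = 14. The assumed drop-out is 20%, and 0.20 × 88 = 17.6, which already exceeds 14. Suspensions therefore come on top of a margin that is fully committed. The effect on power is still small: 44 × 0.80 = 35.2 per arm gives about 79% by t-test, and losing a further 5% of each arm (33.0 per arm) gives about 76%.

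**The case against.** The strongest reply is that little remains once the Section 2.3 and 2.11 events are taken out. No concrete event can be named from the documents that would trigger Section 2.10 alone. That stands, and it is the reason for the low grade.

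A second reply is that to suspend is not to withdraw: a pause lifted before week 24 costs none of these assessments. This also stands. The duration is simply not stated, so a permanent reading cannot be assumed.

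A third is that a condensed article leaves follow-up after discontinuation to the full protocol. This holds only in part. The article does not merely omit a detail; it states a rule at study level, and that wording is what needs changing.

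A reader might also infer that the rule must reach the assessments because controls have nothing else to suspend. Section 2.6 says "The control group will not receive any specific nursing consultations", and Section 2.1 describes controls "who will attend only routine nursing evaluation consultations". On that view half the sample, and the intervention arm for all the weeks after week 16, would be exposed. The documents do not support this. The sentence follows directly on one about effects of the intervention, so it may concern intervention-related risk only. Counting who has no consultations is not counting who would lose data.

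**Conclusion.** The point holds as a minor one. Section 2.10 fixes the suspension at the level of study participation, and no section retains the participant in the 6- and 12-month assessments. Per affected participant the loss runs from nothing, if the suspension is lifted before week 24, to both post-baseline batteries and both evaluation weights, if it starts before week 24 and is not lifted.

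The number affected is unknown and probably very small. Two stronger conclusions should not be drawn. One is that the trial result would be biased: no size or direction can be derived from the documents. The other is that the drop-out margin absorbs these losses: it is already taken up by the assumed 20% drop-out. The same follow-up gap is larger under the drop-out rule in Section 2.3, which is a separate matter.

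**What to change.** Leave unchanged when and why the safety decision is taken. Reword the last sentence of Section 2.10 along these lines: an observed risk suspends the remaining intervention consultations (sessions 1 to 6, weeks 1 to 16), while the already scheduled 6- and 12-month assessments continue unless the participant withdraws consent or the assessment itself would be unsafe.

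The session numbers should be named, because Section 2.5 counts the 6- and 12-month evaluation visits among the eight nursing consultations. A rule that stopped the consultations without saying which ones could still remove the assessments.

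The cost is one sentence. No visit is added. The downside is the small effort of assessing participants who have stopped attending the consultations.
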